## 9. SAFETY REPORTING

### 9.1. Temporary halt for reasons of subject safety

In accordance to section 10, subsection 4, of the WMO, the sponsor will suspend the study if there are sufficient grounds to suggest that continuation of the study will jeopardize subject health or safety. The sponsor will notify the accredited METC without undue delay of a temporary halt including the reason for such an action. The study will be suspended pending a further positive decision by the accredited METC. The investigator will take care that all subjects are kept informed.

### 9.2. AEs, SAEs and SUSARs

#### 9.2.1. *Adverse events (AEs)*

Adverse events are defined as any undesirable experience occurring to a subject during the study, whether or not considered related to the experimental intervention or the trial procedure. All adverse events reported spontaneously by the subject or observed by the investigator or his staff will be recorded. Because primary trial objectives involve a safety assessment, the patients will also be actively asked during all trial visits if any AEs occurred.

#### 9.2.2. *Serious adverse events (SAEs)*

A serious adverse event is any untoward medical occurrence or effect that

- results in death;
- is life threatening (at the time of the event);
- requires hospitalization or prolongation of existing inpatients' hospitalization;
- results in persistent or significant disability or incapacity;
- is a congenital anomaly or birth defect; or
- any other important medical event that did not result in any of the outcomes listed above due to medical or surgical intervention but could have been based upon appropriate judgement by the investigator.
- An elective hospital admission will not be considered as a serious adverse event.

The sponsor will report the SAEs through the web portal *ToetsingOnline* to the accredited METC that approved the protocol. When SAE's have occurred which indicate an inevitable life-threatening risk or which can lead to serious injuries or illness and which require immediate reparative action, the SAE will be reported within 2 workdays and no later than 4 calendar days after the sponsor has first knowledge of the SAE. This includes SAE's which lead to the (temporary) halt of patient inclusion, the (temporary) halt of the study or require changes to be made to the medical device. All other SAE's will be reported within 7 days after the sponsor has first knowledge of the SAE.

#### 9.2.3. *Suspected unexpected serious adverse reactions (SUSARs)*

Since this study does not involve medicinal products, this section is considered to be non-applicable in the case of the current study.

**9.3. Annual safety report**

Since this study does not involve medicinal products, this section is considered to be non-applicable in the case of the current study.

**9.4. Follow-up of adverse events**

All AEs will be followed until they have abated, or until a stable situation has been reached. Depending on the event, follow up may require additional tests or medical procedures as indicated, and/or referral to the general physician or a medical specialist.

(S)AEs need to be reported till the end of study within the Netherlands, as defined in the protocol.

**9.5. Data Safety Monitoring Board (DSMB)**

As requested by the MERC azM/UM, a DSMB will be established to perform an independent interim analysis on preliminary data. The point at which this interim analysis will take place is described in chapter 10.4 of the research protocol (C1). The exact content, tasks and members of the DSMB is described in the DSMB charter (section K5 of the standard research file).

The advice(s) of the DSMB will only be sent to the sponsor of the study. Should the sponsor decide not to fully implement the advice of the DSMB, the sponsor will send the advice to the reviewing METC, including a note to substantiate why (part of) the advice of the DSMB will not be followed.

## 10. STATISTICAL ANALYSIS

The definitive statistical plan will be constructed after data has been collected for the first patient. Below follows the general outline of the statistical plan.

A single-subject repeated measures design will be used whereby each subject acts as their own control. The outcomes of the different parameters (as described in chapter 8.1) will be bootstrapped and descriptively represented by stating mean and standard deviation, median/interquartile range and minimum/maximum values. Due to the small sample size, normality can most likely not be established, therefore non-parametric statistical tests will be performed. Confidence interval will be set at 95%. Due to the small sample size, the outcomes of this trial are not meant to serve as proof for population-wide claims. The goal of the trial is to assess feasibility of chronic vestibular stimulation with a focus on individual effectiveness (compared to within-subject control) and safety, rather than giving definitive statements on its effectiveness as a treatment for a group of patients.

Since the nature of the trial is exploratory and not confirmatory, the choice is made to include a full set of vestibular tests to assess efficacy of the CVI. The data from this trial will be used to be more rigorous in choosing outcome parameters for a future confirmatory trial with a larger population, in order to reduce multiplicity during that trial. Therefore, during this trial no structural statistical steps are taken to control the impact of multiplicities on the type 1 error. However, care will be taken to avoid combining the results of the different outcome measures into one statement on efficacy. DVA will serve as the main primary outcome for VI efficacy due to it giving objective results on the functional restoration of the VOR response pathway. All other parameters will be viewed as auxiliary.

If missing data are observed, the cause of missingness will be ascertained. When the cause of missingness is suspected to be structural, these cases will be described and excluded from analysis of the affected outcome measure. If data is concluded to be missing at random, the imputation strategy will be decided based on the nature and extend of the missingness. In this process the potential for reduced variance caused by interpolation-based imputation techniques will be taken into account. A final imputation strategy will be decided as part of the definitive statistical plan.

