#### 4.4. Sample size calculation

The main outcome parameter of the trial will be DVA (e.g. visual acuity while walking on a treadmill). Regarding the first primary objective (e.g. efficacy of prolonged VI stimulation), a comparison will be made between the condition with the CVI active and the condition with the VI-part inactive (whilst the CI remains active). Visual acuity (VA) can be expressed in several different units. However, for data analysis it is important to use the logarithm of the minimum angle of resolution (logMAR), since this unit scales linearly with the geometric progression of the visual acuity chart .

Data from previous measurements on the influence of the VI on DVA was used for the sample size calculation . Although this data is obtained with a different version of the VI (which a.o. did not allow simultaneous VI and CI stimulation), it is the closest analog available to approximate the results of this trial. To account for the between-patient difference in VA, the data from the previous experiment, expressed in logMAR, were normalized to the static VA measured for each patient. This yields mean logMAR values of 0.065 (SD 0.061) and 0.205 (SD 0.066) for VI active and VI inactive, respectively. Since the size of the dataset is too small to establish whether or not the data is normally distributed, the sample size will be calculated for a two-sided Wilcoxon signed-rank test. Significance level (alpha) is set at 0.05 and power is set at 0.80 . Both effect size and minimal sample size were calculated with G\*Power 3.1.9.7 . Effect size was determined to be 2.20, which resulted in a minimal sample size of 5.

Given the available resources (finances and available implants) and to give this statistical background a safety margin, this trial will aim to include a minimum of 8 patients, with a maximum of 13 patients. If a patient drops out of the trial after implantation, they will not be replaced due to the limited amount of implants that are available. By including at least 8 patients, we will have a safety margin for potential patient drop-outs which will ensure that we will still have enough data to prove a statistically significant change in DVA. By including more patients, we might gain more insight in the role of etiology on stimulation efficacy and interindividual differences in stimulation responses since this still small but

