### 10.1. Primary study parameter(s)

The main comparison of the primary outcome parameters will be between the conditions of VI-OFF and VI-ON. The comparison between these two conditions will be done via an intention-to-treat approach using a Wilcoxon signed-rank test (non-parametric) due to the small sample size and the unlikelihood of being able to proof normality. For this analysis, data from the baseline testing, the prolonged stimulation period and the long-term follow-up will be used. To compare between the different stimulation algorithms, only descriptive statistics will be applied. The lack of statistical power caused by the small sample size does not allow for a multilevel repeated measures analysis of the data.

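### Section 10 bootstraps the outcomes at 8–13 patients without naming the interval type or resampling unit; the common bootstrap intervals for a mean would cover about 88–92%, not 95% (minor)

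*Protocol*

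**What the plan says.** Protocol section 10 states: "The outcomes of the different parameters (as described in chapter 8.1) will be bootstrapped", and in the same sentence that they will be "descriptively represented by stating mean and standard deviation, median/interquartile range and minimum/maximum values". The next sentence chooses non-parametric tests because of the small sample. After it comes a short sentence on its own: "Confidence interval will be set at 95"%. No type of bootstrap interval is named, and the text does not say whether patients or repeated readings within a patient are resampled.

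Section 4.4 fixes the size: "this trial will aim to include a minimum of 8 patients, with a maximum of 13 patients". Section 10.1 gives the main VI-ON/VI-OFF comparison to a test, "using a Wilcoxon signed-rank test (non-parametric) due to the small sample size", and restricts the comparison of stimulation algorithms to descriptive statistics. That comparison is primary objective 1c in section 2.1.

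Section 10 also limits its own reach: "The definitive statistical plan will be constructed after data has been collected for the first patient", and "the outcomes of this trial are not meant to serve as proof for population-wide claims".

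**The concern.** The protocol gives the small sample as its reason for non-parametric methods, yet the usual bootstrap intervals need a larger sample to reach their nominal level. Resampling n patients gives the mean a variance that is too small by the factor (n−1)/n. The percentile and normal-type intervals then also use tails close to the normal rather than the t distribution. Both effects narrow the interval, and at 8 to 13 patients they are not negligible.

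Two parts of the analysis would be exposed. For objective 1a, an interval printed beside the Wilcoxon result could exclude zero when the test does not reject. For objective 1c, the descriptive summaries are the only quantitative analysis planned, so no test stands behind them. In addition, section 10 says the data will inform a later confirmatory trial, and section 4.4 shows a sample size being built on means and SDs from a small earlier dataset. An SD that is biased low would carry forward into such a calculation.

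**Working it through.** The protocol states no coverage figure for the bootstrap, so there is none to reproduce.

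**Inputs.** n = 8 and n = 13 (section 4.4); 95% level (section 10). Assumptions, because the protocol does not fix them: one value per patient, patients resampled, intervals taken from the bootstrap.

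**1. Mean, normal-type interval, normal data.** The bootstrap standard error is s·√((n−1)/n)/√n, so the interval is the mean ± 1.96 times that. Its error rate is 2·P(t with n−1 df > 1.96·√((n−1)/n)).
- n = 8: 1.96 × √(7/8) = 1.833; error 10.9%, coverage 89.1%.
- n = 13: 1.96 × √(12/13) = 1.883; error 8.4%, coverage 91.6%.

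Width relative to the t interval: 1.833/2.365 = 0.78 at n = 8 and 1.883/2.179 = 0.86 at n = 13.

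**2. Mean, simulated coverage** (3,000 samples, 1,000 resamples each):

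| Interval | Normal, n=8 / n=13 | Exponential, n=8 / n=13 | Lognormal, n=8 / n=13 |
|---|---|---|---|
| Percentile | 88.2% / 91.4% | 83.8% / 88.8% | 83.2% / 86.8% |
| Normal-type | 88.5% / 91.8% | 83.6% / 88.2% | 82.8% / 86.4% |
| BCa | 88.4% / 90.8% | 85.9% / 89.9% | 84.7% / 87.4% |
| Bootstrap-t | 94.3% / 94.4% | 93.0% / 94.8% | 92.6% / 92.9% |

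The shortfall therefore depends on the variant. Three common ones fall short and bootstrap-t largely does not.

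**3. SD.** On normal data the average bootstrapped SD is 0.908 of the ordinary sample SD at n = 8 and 0.944 at n = 13, so about 9% and 6% low. A sample size proportional to the variance would be too small by 1 − 0.908² = 18% if it were built on the n = 8 value. This bias does not depend on any choice of interval.

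**4. Minimum and maximum.** A resampled maximum can never exceed the observed one, and equals it with probability 1 − (1 − 1/n)ⁿ: 65.6% at n = 8 and 64.7% at n = 13. No bootstrap variant based on resampling the data repairs this.

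**5. Resampling within a patient instead.** Section 3.2, Table 4 schedules DVA on four days per algorithm week, and Table 2 gives one baseline day. With four readings the formula in step 1 gives 1.96 × √(3/4) = 1.697 on 3 df, error 18.8%, coverage about 81%. With all 12 stimulation readings the error is 8.7%. Both figures assume independent readings, although section 8.1.1 plans to look for adaptation over the stimulation weeks.

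**6. The alternative.** Inverting the exact two-sided signed-rank test, valid for differences symmetric about their centre:
- n = 8: 2·P(W ≤ 3) = 2 × 5/256 = 3.9%, coverage 96.1%.
- n = 13: 2·P(W ≤ 17) = 2 × 196/8192 = 4.8%, coverage 95.2%.

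On normal data this interval is on average about 42–43% (n = 8) and 20% (n = 13) wider than the percentile bootstrap interval. The t interval is wider by 1/0.775 − 1 = 29% and 1/0.864 − 1 = 16%.

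**The case against.** The strongest reply is that these figures describe a procedure that the protocol does not expressly state. The sentence on 95% confidence is separate from the one on bootstrapping and follows the one on non-parametric tests. The bootstrap variant is not named, and bootstrap-t would roughly keep the level. The design is described in single-subject terms ("A single-subject repeated measures design will be used whereby each subject acts as their own control"), so resampling may be meant within a patient. The section is an outline with a fuller plan to follow, and it disclaims population-wide claims. Stating an observed mean, SD, median and range is ordinary description.

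Much of this stands. A reader might infer that the trial's 95% intervals are too narrow; the text does not support that as a fact, because it ties no interval to the bootstrap and leaves bootstrap-t open. A reader might also infer that the main VI-ON/VI-OFF conclusion has an inflated error rate. It does not, since that conclusion rests on the Wilcoxon test. Nor does the text plan an interval for a minimum, a maximum or an SD.

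Three things remain. The commitment to bootstrap is stated, not left open, and the bootstrap is the only procedure named in section 10 that would yield an interval. Within-patient resampling is no escape, because four readings do worse than eight patients. And the absence of a formal decision does not cover objective 1c, which is primary and has only these summaries.

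**Conclusion.** The point holds in conditional form and is minor. If the 95% intervals are percentile, BCa or normal-type bootstrap intervals for a mean, with patients resampled, coverage is about 88–89% at 8 patients and 91–92% at 13 on normal data, and about 83–90% on the skewed distributions tried. With bootstrap-t it is about 94% on normal data. Bootstrapped SDs would be 9% to 6% low, and a bootstrapped minimum or maximum carries no valid inference. The Wilcoxon test is untouched; the intervals reported with it and the descriptive comparison of algorithms are what is exposed. The size rests on the assumed variant, resampling unit and data shape, none of which the protocol gives.

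**What to change.** Replace the bootstrap sentence in section 10, or settle it in the definitive statistical plan, along these lines:
- Use one value per patient. Report each paired contrast (VI-ON minus VI-OFF, and between algorithms) as a Hodges-Lehmann estimate with the interval from inverting the exact signed-rank test, or as a mean with a t interval. The first matches the planned test if that test is run in its exact form, which section 10.1 does not specify.
- Report SD, interquartile range and min/max as observed, without bootstrapping.
- If a bootstrap is kept, resample whole patients, use bootstrap-t, and treat it as secondary.

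The cost is one or two sentences and no extra data. The intervals become wider than percentile bootstrap intervals: by about 29% (n = 8) and 16% (n = 13) for the t interval, and by about 42–43% and 20% for the signed-rank interval. The signed-rank interval also assumes that the paired differences are roughly symmetric.

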#### **8.4. Withdrawal of individual subjects**

Patients can leave the study at any time for any reason if they wish to do so without any consequences. The investigator can decide to withdraw a subject from the study for urgent medical reasons.

As stated in chapter 4.2 and 4.3, patients who make use of VOR suppressing medications will either be asked to stop using this medication before joining the trial (in the case of cinnarizine), or will not be included (in the case of psychiatric medication, e.g. benzodiazepines). However, it can occur that the patient will start taking these medications after they have been included in the trial. If this occurs, it will be noted as a confounder due to the potential effect these medications can have on the VOR response. It will not be seen as a reason for the withdrawal of the patient since the use of these medications does not affect the safety of the patient in the trial and excluding a patient is more detrimental to the usability of the overall data than the potential effect VOR suppressing medications might have. The patients will be notified that they have to inform the research team if they start using VOR suppressing medications (see section E of the standard research file).

Pregnancy is also stated as an exclusion criteria for the trial. However, pregnancy will also not be seen as a reason for the individual withdrawal of a patient. If a patient becomes pregnant, all trial activities which might pose a risk to the pregnancy will be postponed or cancelled until after the pregnancy. Postponing or cancelling will have a smaller influence on the usability of the data gathered in this trial than the

outright withdrawal of a patient. By individually changing the trial schedule there will be no risks for the patient or the pregnancy. The patients will be notified that they have to inform the research team in case of pregnancy (see section E of the standard research file).

Due to the novelty of this study, situations might occur which can cause unforeseen discomfort or side effects for the patient. If this occurs, for example caused by certain stimulation algorithms or measurements, the patient will always have the choice to not undergo a certain part of the trial activities. The planning will then be adapted to this patient specifically to decrease the burden on the patient, and this will not necessarily be seen as a reason for individual patient withdrawal.

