A specific patient will be withdrawn from the regular trial activities if, after multiple fitting attempts, it is established that none of the three vestibular electrodes are able to elicit a vestibular response. This patient will however be offered a detailed examination of potential factors which might have caused this result (e.g. etiology, inner ear and nerve anatomy, electrode placement) and a follow-up plan will be made depending on these results. Unrelated to this follow-up plan, the patient will still receive all the regular care associated with receiving a CI.

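### The main DVA comparison is labelled intention-to-treat, but the exclusion and withdrawal rules limit it to patients with at least one responding electrode and VI-ON data, and handling of declined algorithms is left open

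*Protocol*

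**What the plan says.** On the principle of analysis, section 10.1 states: "The comparison between these two conditions will be done via an intention-to-treat approach using a Wilcoxon signed-rank test". No analysis set is defined.

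On missing data, section 10 splits cases by cause. For the first kind: "When the cause of missingness is suspected to be structural, these cases will be described and excluded from analysis of the affected outcome measure". For the second: "If data is concluded to be missing at random, the imputation strategy will be decided based on the nature and extend of the missingness". The term structural is not defined. Only the imputation strategy is expressly deferred to the definitive statistical plan.

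On withdrawal, section 8.4 has two relevant rules:

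- "A specific patient will be withdrawn from the regular trial activities if, after multiple fitting attempts", it is found that "none of the three vestibular electrodes are able to elicit a vestibular response". Sections 4.4 and 8.5 say that patients lost after implantation are not replaced.
- Where an algorithm or a measurement causes discomfort, "the patient will always have the choice to not undergo a certain part of the trial activities", and "this will not necessarily be seen as a reason for individual patient withdrawal".

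Section 8.2 places randomization after VI fitting. Section 8.3.6 places the VI-OFF baseline day after fitting as well. Section 10.4 acknowledges that some electrodes may give no vestibular response.

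**The concern.** Intention-to-treat normally means that patients are not removed from the comparison for reasons connected with how the treatment worked. Here the foreseeable losses are of that kind: an implanted device that elicits no vestibular response, or stimulation that the patient finds too uncomfortable to continue. A rule that excludes cases on suspected structural grounds, a judgement made once the gap is known, does not sit with the label in section 10.1.

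Two results are affected. The first is the headline gain in DVA, which a reader would take to describe what implantation offers. The second is the descriptive comparison of the three algorithms (objective 1c), where an algorithm that some patients refuse could be summarised only in those who accepted it.

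**Working it through.** **1. The plan's own figure.** Section 4.4 gives normalised logMAR of 0.205 (SD 0.066) with the VI inactive and 0.065 (SD 0.061) with it active.

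- Difference: 0.205 − 0.065 = 0.14.
- Paired effect size: 0.14 / √(0.061² + 0.066² − 2·r·0.061·0.066). The correlation r is not stated. With r = 0.5 the denominator is 0.0636 and the effect size is 2.20, as stated.
- Power is taken from the noncentral t with N scaled by the efficiency of the signed-rank test. With 3/π (normal data) it is 0.784 at N = 4 and 0.932 at N = 5. With the minimum efficiency of 0.864 it is 0.686 and 0.878. Both give N = 5, as stated.

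The sample-size calculation therefore reproduces. The step from 5 to at least 8 is a margin with no stated rate of drop-out or non-response.

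**2. Who reaches the main comparison.** DVA is scheduled on all four days of each stimulation week (Table 4).

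| Patient | Under section 8.4 | VI-ON DVA | Main comparison |
|---|---|---|---|
| No electrode responds | Withdrawn from regular activities | None | Out |
| One or two electrodes respond | Stays | Yes | In |
| Electrodes respond, DVA does not improve | Stays | Yes | In |
| Declines one algorithm | Not necessarily withdrawn | From the other weeks | In; handling of the declined week not stated |

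The set actually analysed is patients with at least one responding electrode who supplied VI-ON data.

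**3. Size.** Assume k of the implanted patients are complete non-responders with no change, and the rest have the planned gain. The estimate after exclusion stays at 0.14. The all-implanted gain is 0.14 × (N − k)/N, and the ratio of the two is N/(N − k).

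| k | All-implanted gain, N = 8 | Excess of 0.14 over it | All-implanted gain, N = 13 |
|---|---|---|---|
| 1 | 0.1225 | 8/7 − 1 = 14% | 0.129 |
| 2 | 0.105 | 8/6 − 1 = 33% | 0.118 |
| 3 | 0.0875 | 8/5 − 1 = 60% | 0.108 |

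**4. Effect on the test.** Suppose complete non-responders enter as exact zeros that keep their place in the ranking (Pratt), and every non-zero change is an improvement. The zeros carry no sign, so the exact two-sided p is 2/2^(8−k): 0.0156, 0.031 and 0.0625 for k = 1, 2 and 3. Excluding them gives the same values. Adding the zeros moves the estimate and leaves the p-value as it was.

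**The case against.** The strongest reply has four parts.

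- **Timing.** Complete non-responders are found at fitting, before randomization and before the baseline day, so omitting them breaches no intention-to-treat principle for a randomized set. That is right as far as it goes. However, randomization only orders the three algorithms. The VI-OFF versus VI-ON contrast is not randomized, so no randomized set defines the label for it, and the protocol names no other set.
- **Outline status.** Section 10 calls itself a general outline with a definitive plan to follow. Detail left to that plan is not a fault. But the exclusion rule and the label are both stated here, and it is these two that conflict.
- **Exploratory purpose.** Section 10 disclaims population-wide claims, and objective 1c is descriptive only. This lowers the stakes but does not remove them. Section 4.4 wants enough data to show a significant change in DVA, and section 11.4.2 ties future trials to success here. Section 8.4 itself keeps users of VOR-suppressing medication in the trial because excluding patients harms the data.
- **Transparency.** Structural cases must be described, so nobody disappears silently. That stands.

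A reader might infer that efficacy is estimated in responders only. The text does not support this: withdrawal needs failure of all three electrodes, and patients with partial response or no DVA gain stay in. The remark in section 10.4 concerns electrodes, not patients. A reader might also infer that patients who refuse stimulation are dropped. Section 8.4 points the other way, and treating their gaps as structural is an inference the text neither makes nor rules out.

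**Conclusion.** The point holds in a limited form. The label in section 10.1 does not match the rules in sections 10 and 8.4, and the resulting estimate describes patients with at least one responding electrode who supplied VI-ON data. Relative to all implanted patients, it is either unchanged or too high, provided the mean gain in the others is positive and complete non-responders truly have none.

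The 14% to 60% range is arithmetic on assumed counts of 1 to 3 in 8. It is not an estimate of the bias to expect: the protocol gives no rate of complete non-response, and with none there is no difference. For declined algorithms the defect is ambiguity, and no direction or size can be given beyond the risk that tolerability is hidden in objective 1c. The stated sample size is not in question here, and neither are the clinical rules on withdrawal and on declining activities.

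**What to change.** Change the wording in sections 10 and 10.1, before stimulation data are seen:

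- Either drop the intention-to-treat label for the analysis with exclusions, or restrict the structural exclusion rule so that it does not apply to DVA missing because of device non-response or discomfort.
- Label the current estimate as applying to patients with at least one responding electrode.
- Report beside it an estimate in all implanted patients, with complete electrode non-responders counted as no change. This needs no extra measurement.
- Use all DVA actually measured in patients who stop or skip a week. Scoring them as zero would discard data and could hide a worsening.
- For objective 1c, give the number declining each algorithm and compare algorithms within patients who have data on both. Ranking a refused algorithm worst would not fit, because the plan has no ranking analysis there.

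The cost is a few sentences and one further line in the results. The reported effect will be smaller if complete non-responders occur. The signed-rank p-value is largely unaffected, so the change corrects the estimate and its interpretation and does not recover power.
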